## Abstract

**Background:**

It is widely agreed that triglyceride (TG)-lowering therapy is imperative in early hypertriglyceridemia-induced acute pancreatitis (HTG-AP). Intravenous insulin with or without heparin, and plasmapheresis are available regimens. However, there is no consensus on first-line therapy.

**Methods/design:**

The Bi-TPAI trial is a multicenter, parallel group, randomized, controlled, non-inferiority trial in patients with early HTG-AP. The Bi-TPAI trial will include 220 patients with HTG-AP from 17 large tertiary hospitals in China. Patients assigned to the intensive insulin group will be administered an intravenous continuous infusion of regular human insulin at a rate of 0.1 units/kg·h and up to 0.3 units/kg·h. Patients allocated to the plasmapheresis group will receive standard-volume plasmapheresis. The primary endpoint is the time it takes for the TG level to reduce to 500 mg/dl. The secondary endpoints are ICU and hospital lengths of stay, 28-day mortality, severity of HTG-AP, incidence of hypoglycemia, HTG-AP complications, and cost-effectiveness.

**Discussion:**

The Bi-TPAI trial will prove that intensive insulin therapy is non-inferior to plasmapheresis. Intensive insulin therapy should be an effective, safe, available, and cheaper triglyceride-lowering therapy for hypertriglyceridemia-induced acute pancreatitis.

**Trial registration:**

ClinicalTrials.gov, NCT03342807. Registered on 5 Nov 2017.

**Electronic supplementary material:**

The online version of this article (10.1186/s13063-019-3498-x) contains supplementary material, which is available to authorized users.

## Background

Hypertriglyceridemia-induced acute pancreatitis (HTG-AP) occurs in the presence of severe hypertriglyceridemia (sHTG) (triglyceride (TG) > 1000–2000 mg/dl) in the absence of other causes [1]. The manifestation of HTG-AP is similar to that of acute pancreatitis (AP) due to other causes. It is usually treated with conservative management and TG-lowering therapy to prevent recurrence of pancreatitis and systemic inflammatory responses, targeting a serum TG level < 500mg/dl [2].

Current guidelines have not yet defined first-line TG-lowering therapies. Previous studies investigating the treatment of HTG-AP with insulin alone, insulin in combination with heparin, plasmapheresis or hemofiltration techniques, and/or fibrates included only case reports and small case series [3–6]. Plasmapheresis can reduce serum TG levels effectively and quickly, but raises concerns about its cost-effectiveness, complications, and staffing resources. Insulin deceases TG by promoting synthesis and activity of lipoprotein lipase (LPL), which hydrolyzes TG into fatty acids and glycerol and facilitates storage of the fatty acids in adipocytes [7]. Enthusiasm for heparin has been waning due to a transient rise in LPL followed by increased degradation and depletion of circulatory LPL [8, 9].

There have been reports where insulin was the main method used for reducing TG levels. However, using an insulin infusion as a therapeutic strategy for lowering TG levels has not yet been adequately studied. No studies have been conducted to identify the better route of insulin delivery (either intravenous or subcutaneous) to treat HTG-AP, although insulin has been used as a continuous infusion in almost all case series and reports. There is also no consensus on the dose of insulin or appropriate ending time. There have been case series or trials targeting euglycemia instead of serum TG level. Diverse insulin strategies yield inconsistent TG-lowering rates. The effectiveness of insulin is underestimated in some studies. We propose using an “intensive insulin therapy in HTG-AP”, which means a continuous insulin infusion until serum TG is < 500 mg/dl, even if the blood glucose level is acceptable.

The Bi-TPAI trial is designed to investigate whether intensive insulin therapy is as effective as plasmapheresis in lowering TG in patients with HTG-AP.

## Methods

### Trial design and setting

The Bi-TPAI trial is a national, multicenter, parallel group, open, non-inferiority, randomized controlled trial that will include 220 patients with HTG-AP, from 17 large tertiary hospitals in China. The Bi-TPAI trial will be conducted according to the principles of the Declaration of Helsinki [10]. The Institutional Review Board of Peking Union Medical College Hospital, Chinese Academy of Medical Sciences & Peking Union Medical College in Beijing, China, approved the trial protocol (version 2.0, reference number ZS-1340, date 20 June 2017). The schedule of enrolment, intervention and assessments following the Standard Protocol Items: Recommendation for Interventional Trials (SPIRIT) guidelines (Additional file 1) is presented in Fig. 1.

**Fig. 1 Fig1:**
[figure not shown]
Standard Protocol Items: Recommendation for Interventional Trials (SPIRIT) schedule of enrolment, intervention and assessments. *Baseline variables: age, gender, body mass index (BMI), diet, history of alcoholism, comorbidity, family history of hypertriglyceridemia or hypertriglyceridemia-induced acute pancreatitis (HTG-AP). ^Primary outcome: triglyceride (TG) level < 500 mg/dl. ^#^Secondary outcome: ICU- and hospital length of stay (LOS), 28-day mortality, HTG-AP severity scores, incidence of hypoglycemia, HTG-AP complications, and cost-effectiveness

### Population

Inclusion criteria are patient age 18–80 years, diagnosis of AP, and TG level > 1000 mg/dl. Exclusion criteria are as follows: (1) other etiology of AP; (2) allergies to plasma, human albumin, and heparin; (3) contraindications for plasmapheresis: mental disorders, circulatory failure, unstable heart or cerebral infarction, intracranial hemorrhage, or severe brain edema; (4) more than 72 h since onset of AP.

There is a research coordinator at each hospital to promote and coordinate the trial. Patients will be informed of the purpose and procedures involved, and the potential risks and benefits of the study. The participants’ written consent will be obtained. Participants will be allowed to withdraw from the trial at any time without consequence.

### Treatment arms and co-interventions

Participants will be allocated to either the intensive insulin group or the plasmapheresis group. The intervention will be started within 24 h after diagnosis in all cases. The intensive insulin group will be administered a continuous intravenous infusion of regular human insulin at a rate of 0.1 units/kg·h and up to 0.3 units/kg·h, titrated to maintain TG < 5.6 mmol/l (500 mg/dl): 5% or higher concentration of intravenous dextrose will be continuously given simultaneously according to fluid and calorie demands. Dextrose infusion is titrated to avoid hypoglycemia and maintain blood glucose levels between 120 and 200 mg/dl (6.7–11.1 mmol/l) during treatment. The plasmapheresis group will receive standard-volume plasmapheresis (1–1.5 plasma volume) every 24 h until the TG level is < 5.6 mmol/l. The plasma volume is calculated as follows:$$ \mathrm{Plasma}\ \mathrm{volume}=0.07\times \left(\mathrm{body}\ \mathrm{weight}\ \mathrm{in}\ \mathrm{kilograms}\right)\times \left(1-\mathrm{HCT}\right) $$

General treatment measures include pancreatic rest (limited oral intake), aggressive intravenous hydration, and analgesia. Patients in the plasmapheresis group who have diabetes mellitus will receive intravenous insulin drips. This insulin will be added in a common ratio with dextrose (generally 1:4~6), aiming to control the patient’s diabetes mellitus with minimal insulin, and not to reduce serum TG.

### Study endpoints

The primary endpoint is the time it takes for tTG to drop to 500 mg/dl. The secondary endpoints are (1) ICU and hospital length of stay (LOS); (2) 28-day mortality; (3) severity of HTG-AP - this will be reported according to the revised Atlanta criteria [11], the Acute Physiology and Chronic Health Evaluation II (APACHE II) score, the Ranson score and computed tomography (CT) grading; (4) incidence of hypoglycemia; (5) HTG-AP complications according to the revised Atlanta criteria [11]; and (8) cost-effectiveness.

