## Discussion

As hypertriglyceridemia may cause more severe acute pancreatitis and worse symptoms, it is imperative to resolve the underlying etiology. There are many available therapies for hypertriglyceridemia-induced acute pancreatitis, including oral lipid-lowering agents, intravenous insulin with or without heparin, and plasmapheresis [13]. Effectiveness, side effects, cost, and availability may influence the final choice of therapy.

Several studies have reported on the effectiveness and safety of insulin [14, 15]. A retrospective cohort study in 2016 showed a significant TG decrease at each time interval in patients treated with intravenous insulin and plasmapheresis, but no difference in clearance rate or length of stay between intravenous insulin and plasmapheresis [16].

A prospective randomized controlled trial (RCT) showed the superiority of high-volume hemofiltration (HVHF) over insulin combined with heparin in lowering TG levels. However, as He, et al. demonstrated in 2016, early HVHF cannot improve clinical outcomes [17]. As for heparin, the effects of heparin on triglycerides are transient because of increased transport of LPL to the liver for degradation [18].

Plasmapheresis is relatively expensive and labor intensive and is associated with complications. Intensive insulin therapy costs much less than plasmapheresis. Researchers calculated that the direct cost to a hospital would be around US$36, if a patient requires 120 units of regular insulin within 24 h. However, a 24-h plasmapheresis course would cost US$3800 plus the variable cost of associated blood products. There is at least 100-fold cost difference between the two therapies [16].

At present, no studies have been conducted to identify the best route (intravenous or subcutaneous) for insulin treatment or the best dose to administer insulin in order to treat HTG-AP. The Bi-TPAI trial plans to include 220 patients from multiple hospitals and should provide adequate power to answer the question of whether intensive intravenous insulin therapy significantly lowers serum TG similarly to plasmapheresis.

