One important limitation of the Bi-TPAI trial is that blinding is not possible due to the nature of the intervention. However, attending physicians and nurses who have no specific interest in the trial will be included. Statistical analysis will be performed in a blinded fashion. We hope to answer the question of whether intensive insulin can effectively reduce serum TG and whether this approach is safe and cost-effective.

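### The only treatment-specific harm among the secondary endpoints is hypoglycemia; plasmapheresis complications, a stated drawback of the comparator, have no endpoint

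*Protocol article*

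**What the plan says.** The secondary endpoints appear three times in the protocol article.

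- Study endpoints (Methods) lists lengths of stay, 28-day mortality and severity, and then "4) incidence of hypoglycemia; (5) HTG-AP complications according to the revised Atlanta criteria [11]; and (8) cost-effectiveness". The numbers (6) and (7) are not used.
- The abstract, after lengths of stay, has "28-day mortality, severity of HTG-AP, incidence of hypoglycemia, HTG-AP complications, and cost-effectiveness".
- The Fig. 1 legend, after lengths of stay, has "28-day mortality, HTG-AP severity scores, incidence of hypoglycemia, HTG-AP complications, and cost-effectiveness".

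The article also says why the comparator is unattractive. According to the Background, plasmapheresis "raises concerns about its cost-effectiveness, complications, and staffing resources". The Discussion repeats this: "Plasmapheresis is relatively expensive and labor intensive and is associated with complications".

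Safety is presented as something the trial will address. The abstract anticipates that "Intensive insulin therapy should be an effective, safe, available, and cheaper triglyceride-lowering therapy", and the Discussion hopes to learn "whether this approach is safe and cost-effective".

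**The concern.** A non-inferiority comparison is of interest because the new treatment may be preferable on grounds other than efficacy. The grounds this article mentions include lower cost, availability, and avoiding the complications of plasmapheresis. Cost has an endpoint. Complications of the procedure do not, while the best-known harm of insulin has an endpoint of its own.

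What is at stake is the safety statement at the end of the trial. With these endpoints, the one table row that reports a named treatment harm will mostly describe insulin. Any statement that insulin spares patients the harms of plasmapheresis would have no prespecified count behind it. The trial is open-label, so procedure events gathered outside a prespecified endpoint, without a common definition and window, would be hard to compare credibly between arms.

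**Working it through.** No figure in the article bears on this point, so the check sets the sections side by side.

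**Step 1. Are the three lists the same?** Yes. Apart from small differences in wording, the abstract, the Fig. 1 legend and Study endpoints each give six items: length of stay (ICU and hospital), 28-day mortality, severity, hypoglycemia, HTG-AP complications and cost-effectiveness. The skipped numbers (6) and (7) could mean that two items were lost from Study endpoints. The other two lists carry no numbers and contain nothing extra, so they do not supply a missing endpoint.

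**Step 2. Classify each item by what it can show about harm.**

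| Item | Type |
|---|---|
| Hypoglycemia | Treatment-specific harm, mainly of insulin |
| HTG-AP complications (revised Atlanta) | Complications of the pancreatitis; may differ in either direction |
| 28-day mortality | Either direction |
| Length of stay | Either direction |
| Severity | Disease measure |
| Cost-effectiveness | Economic; components not defined in the article |

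The count is 1 treatment-specific harm endpoint that is mainly an insulin harm, 0 specific to plasmapheresis, and 3 direction-neutral clinical endpoints that could partly reflect harm in either arm.

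**Step 3. Compare with the stated rationale.** The Background names three concerns about plasmapheresis: cost-effectiveness, complications and staffing. The first has an endpoint. The second, which is the one that concerns patient safety, has none. The revised Atlanta item does not fill the gap, because it is defined as complications of the disease and not of the procedure.

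**Step 4. Is hypoglycemia confined to the insulin arm?** No. Under Treatment arms and co-interventions, "Patients in the plasmapheresis group who have diabetes mellitus will receive intravenous insulin drips". Hypoglycemia can therefore occur in both arms. The article gives neither the expected share of patients with diabetes nor a hypoglycemia rate, so the imbalance in exposure cannot be put in numbers.

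**Step 5. Can the size of the gap be calculated?** No. The article gives no complication rate for plasmapheresis. What can be stated is the count in step 2.

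**The case against.** The strongest counter-argument is that this is a condensed article of protocol version 2.0. Routine recording of adverse events commonly sits in the full protocol, and its absence here shows nothing. That stands, and it limits the point to the endpoint set. It does not remove the point, because the article states that set in full three times with the same content.

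Several stronger readings are tempting, and the article does not support them.

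- A reader might infer that the safety comparison can only go against insulin. It cannot be put that strongly: diabetic patients in the plasmapheresis arm receive insulin, dextrose in the insulin arm is titrated to avoid hypoglycemia, and three clinical endpoints are neutral in direction.
- A reader might infer that procedural harm would be invisible. Serious harm could still show in mortality, length of stay or cost-effectiveness. What is missing is a named, attributable count.
- A reader might infer that the cost analysis leaves out procedure complications. The article does not say which costs or effects enter it, so that exclusion cannot be read from the text.
- A reader might infer that the non-inferiority design rests on the complications of plasmapheresis and fails without them. The article never makes that link explicitly. Cost and availability are also claimed benefits, and cost-effectiveness is an endpoint.

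A further fair objection concerns the remedy. Folding hypoglycemia into a composite of treatment-related events would dilute the main known risk of the experimental treatment, and judging relatedness is subjective in an open-label trial. That stands, and it is why the change should be an addition and not a replacement.

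**Conclusion.** The point holds in a limited form. The stated secondary endpoints contain one treatment-specific harm, mainly of insulin, and none for plasmapheresis, although the article cites plasmapheresis complications as a drawback and asks whether insulin is safe. The named treatment-harm comparison is weighted against insulin, but not exclusively.

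The size is the one-to-none count; no event rate can be attached to it from the article. The primary endpoint, its analysis and the sample size of 220 are not touched. The conclusion assumes that the three matching lists are the intended set and that nothing was lost at the gap in numbering. It makes no claim that the full protocol lacks adverse-event recording.

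**What to change.** - Keep hypoglycemia as a separate secondary endpoint.
- Add to Study endpoints, the abstract and the Fig. 1 legend a further secondary endpoint: treatment- or procedure-related complications, including plasmapheresis procedure-related events.
- Record it over the same window in both arms, and show the event types separately as well as in total.
- Report it as a risk difference with 95% confidence interval. The relative risk named under Statistical methods is a poor summary here: patients given only insulin cannot have a plasmapheresis event, so one arm may have a count at or near zero and the ratio may be undefined or unstable.
- Correct the numbering that jumps from (5) to (8), or restore the items if any were dropped.

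The cost is slightly more data entry and a change of endpoint wording. Recruitment began on 13 June 2018, so for patients already enrolled the events would have to be collected from hospital records. The date of the change should be stated, because the endpoint would be added after recruitment began in an open-label trial.

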### Sample size calculation

The Bi-TPAI trial is a non-inferiority randomized controlled trial. Respective studies and series reported 60–72% of cases with TG < 5.6 mmol/l after one or two sessions of plasmapheresis [4, 12]. A total of 176 participants (88 per group) is required to show non-inferiority of intensive insulin therapy compared to plasmapheresis therapy, with a two-sided significance level of 5% and statistical power of 80%. To account for drop-out and missing data, the sample size is increased by 20% to a final sample size of 220 participates (110 per group).

### Randomization and blinding

Stratified block randomization will be performed centrally in a 1:1 ratio using SAS software (SAS Institute, Inc., Cary, NC, USA). Within each stratum, a random block size of 4 will be used. After written informed consent is obtained, the participant is assigned to one of the two treatment arms. Due to the nature of the investigational treatment, participants and researchers are not blinded to treatment allocation. All analyses will be performed in a blinded fashion.

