### Statistical methods

The primary endpoint will be analyzed based on an intention-to-treat principle, regardless of whether they completed the originally allocated treatment study protocol. Any reasons for protocol violations will be described. All *p* values are two-tailed, and the significance level will be a *p* value <0.05.

Continuous variables will be expressed as means and standard deviations (normal distribution) or median with interquartile range (skewed distribution). Student’s *t* test (normal distribution) or Mann-Whitney *U* test (skewed distribution) will be used for group comparisons. Data will be presented as frequencies and percentages for categorical variables. Categorical variables will be compared using Pearson’s chi-squared test or Fisher’s exact test as appropriate. Time-dependent data will be presented as Kaplan-Meier curves. Statistical uncertainty will be expressed in terms of a relative risk and 95% confidence intervals.

Data will be analyzed using the statistical program SPSS version 20.0 for Windows (SPSS Inc., Chicago, IL, USA).

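### Randomisation is stratified, but the named comparisons are all unadjusted and make no use of entry TG, so the analysis is valid but gives away precision

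*Protocol article*

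**What the plan says.** Under Randomization and blinding, the Protocol article states: "Stratified block randomization will be performed centrally in a 1:1 ratio using SAS software", and adds: "Within each stratum, a random block size of 4 will be used". It does not name the stratification factors.

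Under Study endpoints: "The primary endpoint is the time it takes for tTG to drop to 500 mg/dl". Under Population: "Inclusion criteria are patient age 18–80 years, diagnosis of AP, and TG level > 1000 mg/dl". Entry TG therefore has a floor and no ceiling, and eligibility requires a value from every patient.

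Statistical methods names the comparisons by type of variable:

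- Continuous variables: Student's t test or, for skewed data, the Mann-Whitney U "test (skewed distribution) will be used for group comparisons".
- Categorical variables: "Categorical variables will be compared using Pearson’s chi-squared test or Fisher’s exact test as appropriate".
- Times: "Time-dependent data will be presented as Kaplan-Meier curves".
- Effect measure: "Statistical uncertainty will be expressed in terms of a relative risk and 95% confidence intervals".

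The section names no stratified test, regression model or covariate.

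**The concern.** Two features of the design call for an adjusted analysis, and the named methods use neither.

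First, allocation is balanced within strata. If the strata are prognostic, a test that ignores them keeps between-stratum variation in its standard error although the design has already removed it from the comparison. The test is then conservative.

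Second, the endpoint is the time to an absolute threshold, so a patient who starts higher has further to fall. That makes entry TG prognostic by construction, whatever the treatment.

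The stake is the width of the confidence interval. The trial is planned at 80% power for non-inferiority, where an interval wider than it need be raises the chance of failing to show non-inferiority when it is true.

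**Working it through.** **The plan's own figures.** Sample size calculation gives 176 evaluable patients (88 per group), two-sided 5%, 80% power, and 220 after 20% drop-out. The inflation reproduces: 176 / (1 − 0.20) = 220. The 176 cannot be derived from the stated inputs, because the article gives no margin. One inferred set comes close. With a rate of 66% in both arms (midpoint of the quoted 60–72%), a margin of 20 points and one-sided 0.025, n per arm = 2 × 0.66 × 0.34 × (1.960 + 0.842)² / 0.20² = 88.06. This set is not unique: a log-rank calculation with a hazard ratio of about 1.53 needs 174 events. Nothing below depends on which was used. I take only 88 per arm and 80% power as the anchor.

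**Why entry TG is prognostic.** Assume a constant fractional fall, so that time = ln(TG₀/500)/k. The number of halvings needed is log₂(TG₀/500): 1 from 1000 mg/dl, 2 from 2000 and 3 from 4000.

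**How prognostic.** The article gives neither the distribution of entry TG nor the spread of clearance rates, so both are assumed.

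- Entry TG uniform from 1000 to 2000, 4000 or 6000 mg/dl, with a between-patient CV of k of 0.2–0.8: R² of time on log TG₀ runs from 0.05 to 0.61. It is near or above one half only at a CV of 0.2.
- Entry TG log-normal around 2000 mg/dl (log-SD 0.4–0.6, truncated at 1000), with a CV of k of 0.3–0.7: R² for log time is about 0.15–0.54.
- The same log-normal model, with the outcome reduced to a yes/no reached by 66% of patients: R² falls to about 0.09–0.35.
- The same model, with times in the plasmapheresis arm coarsened to 24-hourly sessions and an assumed fall of 50–80% per session: R² in that arm falls to about 0.10–0.39.

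**What that is worth on a continuous scale.** Adjustment multiplies the standard error by √(1 − R²). With the margin fixed at (1.960 + 0.842) × √(2/88) = 0.422 SD, power = Φ(2.802/√(1 − R²) − 1.960), and n per arm for 80% power is 88 × (1 − R²), rounded up.

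| R² | CI narrower by 1 − √(1 − R²) | Power at 88 per arm | n per arm for 80% |
|---|---|---|---|
| 0 | 0% | 80% | 88 |
| 0.05 | 3% | 82% | 84 |
| 0.10 | 5% | 84% | 80 |
| 0.20 | 11% | 88% | 71 |
| 0.30 | 16% | 92% | 62 |
| 0.50 | 29% | 98% | 44 |

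Over the log-normal range, 0.15–0.54, the interval would be about 8–32% narrower. For the yes/no outcome it would be about 4–19% narrower.

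**Ignoring the strata.** Suppose the strata explain a share R² of the variance and the test ignores them. The actual one-sided error is Φ(−1.960/√(1 − R²)) and the power is Φ(0.842/√(1 − R²)). For R² of 0.10 and 0.30 the error is 0.019 and 0.010 instead of 0.025. Power is 81% and 84%, against 84% and 92% with adjustment. These values are hypothetical, because the factors are not named.

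**On a hazard-ratio scale.** Take the log-normal model with 88 per arm, no treatment effect, an assumed halving time of 12 h and censoring at 72 h. Adding log TG₀ to a Cox model did not reduce the standard error of the log hazard ratio in any of four settings: 0.1526 unadjusted against 0.1542 adjusted, 0.1554 against 0.1565, 0.1525 against 0.1546, and 0.1569 against 0.1579.

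**The case against.** The strongest objection is that covariate choice usually belongs in the statistical analysis plan, which is not shown, and that the article is a condensed account listing tests by variable type. This stands in part: the point can be made only about the methods that the article names. But the article is not silent. It names a set of comparisons, all unadjusted, alongside a stratified allocation. If an unseen plan already adjusts, the two texts only need to be aligned.

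It is also fair to say that nothing here is invalid. A reader might infer that the type I error rate or the sample size is wrong. The documents do not support that: unadjusted tests after stratified allocation keep the error rate at or below its nominal level, and no figure in the plan is shown to be wrong.

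Three further readings go beyond the documents:

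- That entry TG largely determines the time to 500 mg/dl. No figure in the article says so, and under most of the assumptions tried it explains less than half of the variance.
- That the standard error is too large because the strata are ignored. This holds only if the strata are prognostic. If the factor were centre with little centre effect, the loss would be small. If entry TG were itself a stratum, balance on it would already be largely secured.
- That diabetes should join the covariates because plasmapheresis patients with diabetes also receive insulin (Treatment arms and co-interventions). Adjustment would not remove that insulin, so this is a separate question about the contrast between arms.

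The objection about scale stands in full. The √(1 − R²) gain belongs to a linear analysis of an uncensored outcome. In a Cox model, adjustment turns the hazard ratio into a conditional one, and its interval need not narrow.

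**Conclusion.** The point holds as one of efficiency. The article randomises within strata and names only comparisons that use neither the strata nor entry TG, although entry TG is available for everyone and is prognostic for this endpoint.

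The size is uncertain. With R² between about 0.05 and 0.6 on a continuous time scale, the gain runs from about 2 power points to a substantial one. It is smaller for a yes/no outcome or for times coarsened by 24-hourly sessions, and possibly absent for the width of a hazard-ratio interval. All of this rests on first-order decay and on assumed spreads of entry TG and clearance. The part due to the strata cannot be sized. The improvement is worth making because it needs no new data, not because the present tests would mislead.

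**What to change.** In Statistical methods, or in the statistical analysis plan with the article's wording aligned to it:

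1. Name the stratification factors.
2. State that the primary analysis of time to TG below 500 mg/dl accounts for those factors and adjusts for log entry TG.
3. Set the non-inferiority margin on the same scale as that estimate, for example a log-time ratio or an adjusted risk difference. If a Cox model is preferred, state that the hazard ratio is conditional on entry TG, set the margin for that quantity, and do not count on a narrower interval.
4. Report the unadjusted result as a sensitivity analysis.

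The cost is wording only. Entry TG is needed for eligibility and the strata are needed for allocation, so no extra data or patients are required. The change should be fixed before anyone sees outcomes by arm.

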### Trial status

Bi-TPAI trial started recruiting patients on 13 June 2018. Protocol version 2.0 was applied (20 June 2017). The recruitment is expected to be completed before 2021.

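### The only block size given is 4, and it is printed while the open-label trial is recruiting: with hospital strata, up to about 30% of allocations could be known in advance

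*Protocol article*

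**What the plan says.** The article's section on randomization and blinding describes the method in these terms: "Stratified block randomization will be performed centrally in a 1:1 ratio using SAS software". It then fixes the block length: "Within each stratum, a random block size of 4 will be used". No second size is listed and the stratification factors are not named.

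The order of events is also given: "After written informed consent is obtained, the participant is assigned to one of the two treatment arms". The same section states that "participants and researchers are not blinded to treatment allocation", and the section on trial design and setting calls the trial open.

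The trial "will include 220 patients with HTG-AP, from 17 large tertiary hospitals in China". The trial status section dates the start of recruitment to 13 June 2018 and adds: "The recruitment is expected to be completed before 2021". The block length was therefore made public during recruitment.

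Two safeguards are named: a blinded analysis, and (in the Discussion) attending staff who have no particular stake in the trial.

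**The concern.** A single size means a fixed block. In an open trial of two treatments that nobody can mistake for each other, staff know which arm each past patient received. Someone who knows the block length and the earlier allocations in a stratum knows the fourth assignment of every block, and also the third whenever the first two match.

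Assignment follows consent, so whoever approaches patients could foresee the arm before deciding whether to offer the trial. Central allocation hides the list, but not what past assignments imply about the next one. Blinded analysis acts only after enrolment.

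The primary endpoint makes this relevant. It is the time for triglyceride to fall to 500 mg/dl. Entry requires a level above 1000 mg/dl and sets no upper limit. Baseline triglyceride is known at enrolment and plausibly drives the endpoint, so selective enrolment on it could distort the comparison.

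**Working it through.** The plan states no predictability figure, so there is none to reproduce first.

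**Inputs.** Block length 4, ratio 1:1 and open allocation (randomization and blinding); 220 patients and 17 hospitals (trial design and setting). Assumption, not in the documents: the observer knows the block length, where each block starts, and every earlier allocation in the stratum.

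**Certain allocations in a complete block.** Two A and two B can be ordered in 6 equally likely ways.
- Positions 1 and 2 are never certain.
- Position 3 is certain when the first two match (AABB, BBAA): 2/6 = 1/3.
- Position 4 is always certain: 1.
- Share = (0 + 0 + 1/3 + 1)/4 = 8/24 = 33.3%.

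**Best guess (name the arm with more places left).** The chance of being right is 1/2 at position 1, 2/3 at position 2, 1/3 × 1 + 2/3 × 1/2 = 2/3 at position 3, and 1 at position 4. The mean is (1/2 + 2/3 + 2/3 + 1)/4 = 17/24 = 70.8%, against 50% by chance.

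**Incomplete last blocks.** 220/17 is about 13 patients per hospital: three full blocks and one further patient, who is never predictable. Each full block contains 4/3 certain allocations, so a site has 3 × 4/3 = 4, and 17 × 4 = 68, or 68/220 = 31%. A simulation that spreads 220 patients at random, with equal probability, over the strata gives:

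| Strata | Certain share | Patients of 220 |
|---|---|---|
| 17 (hospital only) | 30% | 66 |
| 34 | 27% | 59 |
| 68 | 20% | 44 |
| 136 | 10% | 21 |

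**Alternatives.** For an observer who knows which sizes are possible but not which one is in use:

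| Scheme | Certain share |
|---|---|
| Fixed 4 | 33.3% |
| Fixed 6 | 25.0% |
| Fixed 8 | 20.0% |
| 4 and 6 mixed at random | 5.5–5.8% |
| 4, 6 and 8 mixed at random | about 2.3% |

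The two mixed rows come from simulation. Mixing sizes mainly removes certainty; it does not end guessing. Even fixed blocks of 6 leave a best-guess rate of 68.3%.

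**The case against.** The strongest objection is that the strata are unnamed. If they are clinical categories that span hospitals, a recruiter at one of 17 sites sees about 1/17 of a stratum's sequence on average and can be certain of very little. This stands, and it makes the size of the problem conditional.

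The wording may also be loose language for randomly permuted blocks of length 4, an ordinary method. That is a fair reading and it removes any charge of self-contradiction. It leaves the length fixed and public.

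Opportunity to exploit a prediction is limited. Onset must be within 72 h and treatment must start within 24 h of diagnosis. About 13 patients per site over some 30 months (mid-June 2018 to the end of 2020) is one every 30/13, or about 2.3, months. There is no queue to reorder, so timing enrolment is hardly feasible. Choosing whom to approach remains possible.

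The named safeguards deserve mention, and it would be wrong to say that nothing is blinded. But blinded analysis cannot undo selective entry, and the remark about disinterested attending staff does not say who recruits.

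A reader might infer that a third of the sample, 220/3 or about 73 patients, is predictable. That would need every block to be complete and every sequence to be visible. About 13 patients per site rules out the first, and the article does not establish the second. A reader might also infer that steering would favour insulin and so non-inferiority. Nothing in the article indicates a direction; the reverse is equally possible.

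**Conclusion.** The point holds in conditional form. As written, one block length of 4 applies within strata, and it was disclosed during open recruitment. If the strata include the hospital, or the sequence is otherwise visible to recruiters, about 30% of allocations (66 to 68 of 220) can be known beforehand with 17 site strata, and fewer with more strata. The 33% figure is a ceiling for complete blocks. If strata cross hospitals, one site can predict far less.

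These figures assume roughly equal recruitment across strata and full knowledge of earlier allocations. They measure opportunity for selection bias. They do not show that bias occurred, how large it would be on the primary endpoint, or which arm it would favour. It is a cheap improvement to make and does not by itself invalidate the trial.

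**What to change.** 1. For all remaining allocations, have the central statistician use randomly varying block sizes (for example 4 and 6), neither disclosed to sites nor published until recruitment ends.
2. Correct the sentence in the randomization and blinding section. It should say plainly that the allocations made so far used permuted blocks of fixed length 4, if that is what was done, and that later ones use varying sizes, without listing the sizes while recruitment continues.
3. For patients already enrolled, test whether baseline triglyceride and severity are associated with the predicted arm, as in a Berger-Exner analysis. The predictor is the probability of assignment to insulin given earlier allocations in the stratum: insulin places left divided by all places left in the block. It takes the values 0, 1/3, 1/2, 2/3 or 1. Do not compare baseline values by position in block: later positions are equally likely to be either arm, so steering would tend to cancel and the check could falsely reassure.

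The cost is regenerating the unused part of the central list and a slightly larger possible imbalance within small strata. The third step needs only the order of allocation by stratum and the baseline data. If recruitment has already closed, the second and third steps still apply, and the corrected sentence then simply reports what was done.
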